#### (3) MI training

All direct SUDT service providers and workgroup supervisors in both conditions are eligible to receive training in MI. This entails a one-time, 2-day training that occurs approximately 1 week to 1 month after the beginning of the LOCI leadership trainings. The first day addresses basic MI skills, and the second day addresses intermediate MI skills. MI training typically includes didactic training on topics such as the spirit and principles of MI and interactive training and interactive exercises in order to provide skill building and practice. MI trainers are Motivational Interviewing Network of Trainers (MINT) members.

#### (4) MI fidelity data collection

Participants will be asked to audio record and upload all of their sessions with clients where MI could be utilized. A digital audio recorder will be provided for each direct service provider. Although clients receiving the MI intervention may be heard on the audio recordings of these MI sessions, clients themselves will not be participants in the study. The research team will receive no identifying information about clients, and although no identifiable client information will be collected, informed consent will be sought from clients stating that they will allow the audio recording of their sessions. After audio recording MI sessions, participating service providers will log into a secure, HIPAA-compliant file-sharing website to upload each audio file. One randomly selected recording per counselor per month will be coded for fidelity, and a fidelity report for each provider will be provided back to the supervisor. Supervisors have the additional option of receiving individual training on providing fidelity feedback and coaching for direct service staff.

### Data collection and management

Data are to be collected at baseline (prior to the interventions), 4, 8, 12, and 16 months (4 months after the end of the LOCI intervention). Organizational data will be collected from all participants (service providers, workgroup supervisors, and executives/mid-managers) via web surveys and downloaded into a database programmed for error identification and checking. Each type of respondent will complete a set of measures in their survey, and not all measures will be collected at each time point. The provider/supervisor surveys will take about 20–30 min to complete, whereas the survey for executives/mid-managers will take about 5–10 minutes per supervisee. Participants will be compensated with a $25 electronic gift card via email for completing each survey. A portion of the data collected in these surveys (i.e., FRL, implementation leadership, EBPAS, EBP implementation climate) will be shared with supervisors in the LOCI condition as a part of the leadership development intervention. Data from managers/executives will be shared with the supervisors, and this is comparable to a typical performance review. Data from service providers will be shared with their supervisors in an aggregate manner to protect the confidentiality of individual provider responses. All data will be stored on a secure server with incremental and weekly full back up.

### Measures

#### Demographics

Data to be collected includes age, sex, education level, professional status (e.g., intern vs. professional), and job tenure [13].

#### Full-range leadership

The Multifactor Leadership Questionnaire (MLQ) [70] assesses transformational and transactional leadership. MLQ scores are associated with organizational climate and working alliance in behavioral health agencies [71] and predict organizational effectiveness. Service providers rate the extent to which their immediate supervisor engages in specific behaviors measured by the MLQ, and executives do the same for their supervisees. Each behavior is rated on a 5-point scale (0 = Not at all, 4 = Frequently, if not always). The MLQ has good to excellent psychometric properties with Cronbach’s alphas ranging from .76 to .90. Transformational leadership is assessed by four subscales: Idealized Influence (8 items, *α* = .87), Inspirational Motivation (4 items, *α* = .91), Intellectual Stimulation (4 items, *α* = .90), and Individual Consideration (4 items, *α* = .90). Transactional leadership is assessed with two subscales of Contingent Reward (4 items, *α* = .87) and Active Management-by-Exception (4 items, *α* = .74).

#### Implementation leadership

The Implementation Leadership Scale (ILS) is a brief measure of unit level leadership for EBP implementation with excellent reliability and convergent and discriminant validity [23]. The four ILS subscales are Proactive Leadership (*α* = .95), Knowledgeable Leadership (*α* = .96), Supportive Leadership (*α* = .95), and Perseverant Leadership (*α* = .96), and the total score is *α* = .98. Each item is scored on a 5-point Likert-type scale (0 = Not at all, 4 = To a very great extent).

#### Implementation climate

The Implementation Climate Scale (ICS) [30] was adapted from Klein and colleagues’ study of innovation implementation [31] and considering Schein’s construct of “embedding mechanisms” [2]. The ICS assesses employees’ shared perceptions of the policies, practices, procedures, and behaviors that are expected, supported, and rewarded to facilitate effective EBP implementation. All items are scored on a 5-point Likert-type scale (0 = Not at all to 4 = To a very great extent). The ICS has excellent internal consistency and convergent and discriminant validity. The ICS has an overall Cronbach’s alpha of .91 (18 items, 3 items on each subscale). The six subscales are Focus on EBP (*α* = .91), Educational Support for EBP (*α* = .84), Recognition for EBP (*α* = .88), Rewards for EBP (*α* = .81), Selection for EBP (*α* = .89), and Selection for Openness (*α* = .91).

#### Psychological safety climate

Psychological safety climate (PSC) will be assessed with the PSC scale [72], which assesses employees’ shared perceptions of organizational policies, procedures, and behaviors regarding a supportive, safe work environment for taking interpersonal risks. The PSC has seven items scaled from 0 (Doesn’t apply at all) to 4 (Entirely applies) with good internal consistency reliability (*α* = .82), construct, and concurrent validity. PSC scores are associated with workgroup membership, contextual support, and interactions with the workgroup supervisor.

#### Attitudes toward EBP

The Evidence-Based Practice Attitude Scale (EBPAS) [73] will assess individuals’ attitudes toward EBP. The EBPAS has 15 items with four subscales that assess attitudes toward adoption of EBP as a function of perceived *Appeal* of EBP, *Requirements* to use EBP, provider *Openness*, and perceived *Divergence* between EBP and usual care. EBPAS total scores (*α* = .76) represent global attitudes toward adoption of EBP and subscale alphas range from .66 to .91. EBPAS responses are scored on a 5-point scale (0 = Not at all, 4 = To a very great extent), and scores are associated with individual provider-level attributes and organizational characteristics [73–75].

#### EBP Implementation Citizenship Behavior

The Implementation Citizenship Behavior Scale (ICBS) [69] will assess individual EBP implementation citizenship. The ICBS was adapted from an existing measure of safety citizenship in the workplace [76] and assesses the extent to which individual workgroup members go beyond minimum requirements to support successful EBP implementation in regard to helping others and keeping informed. The ICBS is comprised of 6 items that are scored on a 5-point scale (0 = Not at all, 4 = Frequently, if not always). The ICBS has demonstrated excellent internal consistency reliability for the Helping (*α* = .93, 3 items), Keeping Informed (*α* = .91, 3 items), and ICBS Total EBP Citizenship scales (*α* = .93).

#### Assessment of Prior MI Use

The Assessment of Prior MI Use measure was developed for this study to measure the extent to which service providers have been exposed to MI (i.e., previoustraining and use of MI with clients) prior to the MI training offered as a part of the study. All participants will be asked about prior training and current use of MI, in addition to study data on number of recordings and session uploads, to aid in determining penetration at provider and client levels. Those with prior experience are asked to estimate the percentage of clients with whom they use MI and the extent to which they use MI with fidelity. These data can be used as provider-level covariates in quantitative analyses.

#### LOCI Component Assessment

The LOCI Component Assessment was developed to increase understanding of the relative importance and utility of each of the six components of LOCI. It measures the extent to which LOCI trainees perceive each component to be important and useful in achieving change in leadership and improving EBP implementation.

#### MI Coach Rating Scale

The MI Coaching Rating Scale (MI-CRS) [77] will be used to assess fidelity. This scale was developed based on the MI Treatment Integrity Instrument (MITI) [78] that has demonstrated inter-rater reliability and differentiates between MI and usual care [79]. The MI-CRS was developed utilizing Item Response Theory [80, 81] and is designed to be useful for research and practical for agencies to utilize for their own in-house fidelity monitoring. Five items address the relational components of MI, and 5 items address the technical components of MI, with each item scored on a 4-point scale (1 = Poor, 2 = Fair, 3 = Good, 4 = Excellent). A mean of 3.5 and above on a given component is considered solid competence, a mean of 2.5 to 3.5 is considered beginner competence, and a mean score of less than 2.5 is considered below competence. Component scores will be averaged to compute a total mean fidelity score. Research staff will use the MI-CRS to code audio recordings of client sessions in which MI is used.

#### Stages of Implementation Completion

The stages of implementation completion (SIC) measure will be used to assess implementation process [82]. It assesses activities that occur during eight stages of the measure, which fit within the EPIS implementation phases of Preparation (e.g., SIC pre-implementation) and Implementation. The SIC will be adapted for MI and LOCI to assess each workgroup’s progress toward successful MI implementation in consultation with the measure developer, and completed by the investigative team based on ongoing documentation of the dates at which each SIC activity and stage is completed. Three scores are calculated: (1) a duration score (i.e., time in days that a site takes in a stage), (2) proportion score (i.e., percentage of activities completed within a stage), and (3) the SIC stage score (i.e., number of stages completed). The SIC has demonstrated construct and predictive validity and identifies and predicts variation in implementation process [83, 84].

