### Significance

There are two main potential impacts of the proposed study. First, improving leadership and organizational climate for EBP will advance both implementation science and will provide an empirically tested implementation strategy to decrease the lag between intervention or innovation development and deployment and sustainment in usual care settings [66]. Demonstrating the efficacy of LOCI will provide service systems and health care organizations with a way to simultaneously improve leadership and institute organizational strategies to support and promote effective EBP implementation and sustainment. Second, although counselors and clinicians may receive training in MI, leaders and organizations often do not apply strategies to effectively implement MI or support staff to deliver MI with fidelity beyond initial training [67, 68].

To our knowledge, there are no other empirically tested workgroup level approaches that bring together leadership and organizational strategies to improve strategic climate for EBP and implementation effectiveness. In addition, this proposed study utilizes new reliable and valid measures of implementation leadership [23], implementation climate [30], and implementation citizenship [69] and will apply the Stages of Implementation Completion (SIC) measure [37] to assess LOCI and MI implementation process.

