## Methods

This study will test the effects of LOCI in facilitating MI implementation in SUDT service settings.

The study’s aims and hypotheses are:Aim 1: Conduct a cluster, randomized trial to test the effects of LOCI vs. webinar control condition on full-range leadership and implementation leadership behaviors.H1a: Provider-rated FRL will improve more in the LOCI vs. control condition.H1b: Provider-rated implementation leadership will improve more in the LOCI vs. control condition.
Aim 2: Test the effect of LOCI on workgroup level implementation climate and psychological safety climate, provider-level attitudes toward MI, and provider implementation citizenship behaviors.H2a: Implementation climate will show greater improvement in LOCI vs. control leader workgroups.H2b: Psychological safety climate will show greater improvement in LOCI vs. control leader workgroups.H2c: Providers in LOCI vs. control condition will report more positive attitudes to MI.H2d: Providers in LOCI vs. control condition will demonstrate greater implementation citizenship.
Aim 3: Test the effect of LOCI on implementation outcomes MI fidelity and implementation process.H3a: Workgroups in LOCI vs. control condition will show greater improvement in MI fidelity.H3b: Workgroups in LOCI vs. control condition will show greater implementation efficiency as measured by the SIC.
Aim 4: Explore mediational and cross-level effects (e.g., effects of workgroup level climate on provider attitudes) and test the effects of leadership and strategy on implementation climate, subsequent effects on attitudes toward EBP, and implementation citizenship. Example hypotheses include:H4a: More positive workgroup level implementation climate will be associated with more positive provider-level attitudes toward EBP and implementation citizenship behaviors.H4b: More positive workgroup level psychological safety climate will be associated with more positive provider-level EBP attitudes and implementation citizenship behaviors.H4c: Implementation climate will mediate the effects of leadership on attitudes toward EBP and implementation citizenship behaviors.H4d: Provider attitudes toward EBP and implementation citizenship will mediate the effects of implementation climate on fidelity.

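### H3b compares the arms on an SIC adapted to LOCI as well as MI, without limiting the comparison to activities both arms can complete

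*Protocol article*

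**What the plan says.** Under Aim 3 in Methods, H3b is a comparison between arms: "Workgroups in LOCI vs. control condition will show greater implementation efficiency as measured by the SIC".

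The section Stages of Implementation Completion describes the instrument: "The SIC will be adapted for MI and LOCI to assess" how far each workgroup has come in implementing MI. It is "completed by the investigative team based on ongoing documentation" of the dates on which activities and stages are finished. It has eight stages and yields three scores: days spent in a stage, a "proportion score (i.e., percentage of activities completed within a stage"), and a count of stages completed. The Significance section gives the same double scope, saying that the SIC will be applied "to assess LOCI and MI implementation process".

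LOCI's training, coaching and organizational strategy meetings are set out under LOCI intervention. Under Webinar condition, control supervisors are given four one-hour webinars. MI training is offered in both arms. The Data analyses section plans negative binomial regression for workgroup-level counts of implementation process and does not say which SIC activities are counted.

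**The concern.** An outcome that compares randomized arms should contain only what both arms had the chance to achieve. Here the outcome measure for H3b is described, in two places, as covering the tested intervention as well as the practice being implemented. A control workgroup is offered no LOCI training, coaching or strategy meeting, so it cannot complete such an activity, however well it implements MI.

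If those activities count in the compared score, the LOCI arm gains credit for having received LOCI. If each arm is instead scored on its own list, percentages and stage counts rest on different denominators. In either case H3b would no longer isolate its intended question, which is whether LOCI makes MI implementation more efficient. H3b is one of the two Aim 3 hypotheses, so the reading of that aim is at stake.

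**Working it through.** The article gives no SIC activity counts and no power calculation for H3b, so there is no figure of its own to reproduce. The check is a reading of the passages, followed by an illustration with assumed inputs.

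**Reading.** The comparison is between arms (H3b). The instrument covers MI and LOCI (Stages of Implementation Completion; Significance). LOCI components are described for one arm only (LOCI intervention; Webinar condition). No section says whether LOCI activities are scored, left out or marked not applicable for control workgroups.

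**Proportion score.** Let f be the LOCI-only share of activities, and let p be the completion probability for any activity open to a workgroup, equal in both arms (no true MI difference). If LOCI-only activities stay in the control denominator:

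- control ceiling = 1 − f
- expected score: LOCI = p, control = p(1 − f)
- built-in difference = p − p(1 − f) = p × f

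For example, p = 0.6 and f = 10% gives 0.6 × 0.10 = 6 points; p = 0.8 and f = 20% gives 0.8 × 0.20 = 16 points.

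**Chance of a false positive.** The documents supply 60 workgroups, split equally, so 60 / 2 = 30 per arm. All else is assumed: 40 activities, completion varying between workgroups (beta-binomial, correlation 0.1), a two-sided t-test at 0.05 on the overall proportion completed, and 4,000 runs per setting.

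| f | control ceiling | built-in difference (p = 0.6; 0.8) | chance of a significant result favouring LOCI (p = 0.6; 0.8) |
|---|---|---|---|
| 5% | 95% | 3; 4 points | 10%; 20% |
| 10% | 90% | 6; 8 points | 28%; 63% |
| 20% | 80% | 12; 16 points | 82%; >99% |
| 30% | 70% | 18; 24 points | >99%; >99% |

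At f = 0, which is a list common to both arms, the total false-positive rate is 5.2% (p = 0.6) and 5.1% (p = 0.8), close to nominal. The illustration pools all activities. The article's proportion score is defined within a stage, so in practice f would apply stage by stage and be larger wherever LOCI activities are concentrated.

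**Stage score.** If k of the eight stages cannot be completed without a LOCI-only activity, the control maximum is 8 − k. If no stage depends on such an activity, k = 0 and there is no cap. The article does not give k.

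**Duration score.** Extra LOCI activities could lengthen a stage in the LOCI arm and so count against LOCI. No direction can be assigned.

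**The case against.** The strongest reply is that the sentence on adapting the SIC goes on to name progress toward MI implementation, in each workgroup, as the target. A measure aimed at MI progress, with LOCI tracked separately where it is delivered, fits both that sentence and the one under Significance. The activity list, the handling of inapplicable items and the scoring subset would normally sit in the adapted instrument or the analysis plan, which are not shown. Leaving them out of an article is no error.

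Much of this stands. A reader might infer that H3b is partly true by construction. The documents do not support that: no section says control workgroups are scored on LOCI activities, the stage score is capped only under a completion rule the article does not state, and the duration score, arguably the one closest to efficiency, need not favour LOCI. A reader might also infer that records are denser in the LOCI arm because of the weekly coaching calls. That is a guess. The article does not name the calls as a source for the SIC, and MI training, session uploads and monthly fidelity coding are described without a difference between arms.

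What the reply does not remove is the pairing that the article itself fixes. Stating MI progress as the purpose does not take LOCI out of the content. The article describes one eight-stage instrument with three scores, mentions no MI-only score, and assigns that instrument to a comparison between arms. Read literally, this lets activities that only one arm can complete into the outcome. That is a matter of scope stated in the article, not just of missing detail.

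**Conclusion.** The point holds in conditional form. The article adapts the SIC to LOCI as well as MI, and H3b compares arms on it with no limit to shared activities. If LOCI-only activities enter the compared score, the control proportion score is capped at 1 − f and a positive result may show only that LOCI was delivered. Even a modest share would matter with 60 workgroups: under the assumptions above, f = 10% produces a significant result favouring LOCI in 28% to 63% of runs with no true MI difference.

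The actual size is unknown. It depends on f and on a scoring rule, neither of which the article gives. If the comparison is already confined to common MI activities, this bias is absent and only the wording needs correcting.

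**What to change.** State in Stages of Implementation Completion and in H3b that the between-arm SIC scores use one common list of MI activities and stages open to both arms, with stage completion defined on that list. Require completion dates to be documented in the same way in each arm. Report LOCI activities separately and descriptively, as intervention delivery within the LOCI arm.

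This takes a sentence or two and a scoring subset. LOCI items are still collected, so no data are lost. The downside is a slightly narrower H3b score.

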#### Assessment of Climate Embedding Mechanisms (ACEM)

The ACEM was developed for this study and will be used to measure the organizational strategies developed and used by each organization and leader trainee. The first part of the measure includes qualitative items to identify all strategies that are being used within a workgroup, the larger organization, and across levels to embed a climate for the implementation of MI. For each strategy identified, quantitative items measure each strategy’s frequency of use and level of emphasis. The result is a list of strategies used within each workgroup and organization to support the implementation of MI.

#### LOCI Feasibility, Acceptability, Utility

The LOCI Feasibility, Acceptability, Utility scale [1] is an 11-item measure developed for the LOCI pilot study to assess the LOCI training.

### Data analyses

The study will obtain estimates of the leadership intervention effect by comparing multiple intervention measures on provider-rated leadership, workplace climate, work attitudes, and attitudes toward adopting and implementing EBPs. The workgroup will be the unit of analysis, with sites randomized within agency to ensure that the 5% of co-located workgroups will be randomized into the same condition to avoid contamination. For 95% of workgroups, workgroup is synonymous with site. We will stratify by the number of workgroups per site to ensure equal workgroups in each condition.

Data analytic strategies will follow the recommendations of Brown et al. [85] and the Prevention Science and Methodology Group for randomized field trials [86]. Preliminary data screening and cleaning will require examination of data distributions for normality and missing data patterns at both the univariate and multivariate levels. Once complete, hierarchical linear modeling (HLM) [87] will be used as the primary statistical model due to the nested structure of the data: repeated measures (time) (level-1) nested within service providers (level-2) nested within workgroups (level 3). Because randomization is at the workgroup level, and due to the statistical complications associated with the small number of agencies and a number of workgroups being located at the same site, dummy-coded agency and site variables will be entered at the level of the workgroups for all analyses, which implicitly controls for agency and site effects [88]. Random effect variance will be evaluated for the remaining levels of the nested data structure. In the presence of near zero estimates of variance estimates, terms will be removed from the statistical model.

HLM analyses for aims 1 and 2 will test specific intervention effects (LOCI vs. webinar control condition) on target outcomes (e.g., leadership behaviors, implementation climate). Of primary interest in these analyses is the Time (level-1) × Intervention Status (level-3) cross-level interaction effect. If the cross-level interaction term(s) are statistically significant, follow-up examination of these effects will follow the procedures of Preacher, Curran, and Bauer [89]. Implementation of cross-classified models will be explored given that some shifting or personnel may occur during the course of the study [90].

Aim 3 will test fidelity. The statistical methods used will be based on the HLM models described for the first two aims; however, since measurements for this outcome are averaged over time, there will not be a modeled covariance structure. For count outcomes related to implementation process (workgroup level), we will use a negative binomial regression model instead of a Poisson regression model to allow for the possibility of over-dispersion.

Finally, mediational effects described in aim 4 will use procedures for multilevel data structures outlined in MacKinnon [91]. For all analyses, covariates will be considered at both the provider and workgroup level. Inclusion of confounder variables at the provider level is important given that randomization to LOCI vs. control condition will not occur at this level. Inclusion of covariates at the workgroup level will adjust for chance imbalances and increase the precision of the analyses.

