**Methods:**

This test of the LOCI intervention will take place in conjunction with the implementation of motivational interviewing (MI) in 60 substance use disorder treatment programs in California, USA. Participants will include agency executives, 60 program leaders, and approximately 360 treatment staff. LOCI will be tested using a multiple cohort, cluster randomized trial that randomizes workgroups (i.e., programs) within agency to either LOCI or a webinar leadership training control condition in three consecutive cohorts. The LOCI intervention is 12 months, and the webinar control intervention takes place in months 1, 5, and 8, for each cohort. Web-based surveys of staff and supervisors will be used to collect data on leadership, implementation climate, provider attitudes, and citizenship. Audio recordings of counseling sessions will be coded for MI fidelity. The unit of analysis will be the workgroup, randomized by site within agency and with care taken that co-located workgroups are assigned to the same condition to avoid contamination. Hierarchical linear modeling (HLM) will be used to analyze the data to account for the nested data structure.

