### Design

Multiple study designs were considered by the research team in consultation with collaborating agencies. In order to reduce participant burden, a multiple cohort design, cluster randomized trial that randomizes workgroups within agency to either LOCI or a webinar control was selected. Allocation was determined by the statistician on the project. Three consecutive cohorts of participants will be included. The LOCI intervention lasts for 12 months and the webinar control intervention takes place in months 1, 5, and 8 for each cohort. The unit of analyses will be workgroup, randomized by site within agency with care taken that co-located workgroups are assigned to the same condition to reduce the chances of contamination.

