#### Inclusion criteria

Participants for the proposed study will fall into three groups: (1) SUDT service providers (i.e., “service providers” *n* = 360), (2) SUDT workgroup supervisors (i.e., “workgroup supervisors” *n* = 60), and (3) SUDT agency executives and managers (i.e., “executives/managers” *n* = 60), total *N* = 480.

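### A dummy for every site makes the LOCI effect on fidelity and SIC counts (Aim 3) inestimable, because LOCI is randomized by site

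*Protocol article*

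**What the plan says.** Allocation is by site. The Design section has workgroups "randomized by site within agency with care taken that co-located workgroups are assigned to the same condition", and the Data analyses section repeats the rule, "with sites randomized within agency to ensure that the 5% of co-located workgroups will be randomized into the same condition". It adds: "For 95% of workgroups, workgroup is synonymous with site".

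The same section then fixes the adjustment: "dummy-coded agency and site variables will be entered at the level of the workgroups for all analyses". The reasons given are the small number of agencies and the fact that some workgroups share a site. Random-effect variances are to be examined for the levels that remain.

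For Aims 1 and 2 the target is an interaction: "Of primary interest in these analyses is the Time (level-1) × Intervention Status (level-3) cross-level interaction effect". For fidelity in Aim 3, "The statistical methods used will be based on the HLM models described for the first two aims", but the outcome is averaged over time. SIC counts are analysed at workgroup level by negative binomial regression. No time term is described for either Aim 3 model. Nothing exempts Aim 3 from the site dummies or limits the dummies to shared sites.

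**The concern.** A covariate that is constant within sites carries no information once every site has its own intercept. LOCI status is such a covariate. In Aims 1 and 2 this does little harm, because the question is whether slopes over time differ by condition and the dummies act on the intercept. In Aim 3 the LOCI effect is itself a between-site difference, which is what a full set of site dummies removes.

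At stake are H3a and H3b, the fidelity and implementation-process hypotheses. An analyst following the literal text would meet a singular model. They would then have to change it after data collection, without a planned rule for doing so. If a column were dropped to make the model fit, the coefficient labelled LOCI would be a contrast between particular sites.

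**Working it through.** The article gives no power, alpha or sample-size figure for this point, so there is nothing to reproduce. The question is identifiability, which can be settled by algebra and checked by matrix rank.

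**Inputs from the article**
- 60 workgroups and about 360 providers (Abstract, Methods: "Participants will include agency executives, 60 program leaders, and approximately 360 treatment staff"), so 360 / 60 = 6 providers per workgroup.
- About 5% of workgroups co-located: 0.05 × 60 = 3.
- Condition constant within site (Design; Data analyses).

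**Assumptions, because the article does not give them**
- Number of agencies: 5, 10 or 15.
- Co-location pattern: one site of 3, or one, two or three sites of 2.
- One SIC record per workgroup.
- Half the sites in each agency (rounded down) assigned to LOCI.

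**Algebra.** Let t_s be the condition of site s and D_s its dummy, with site 1 as reference. Because condition is constant within site,

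LOCI = t_1 × 1 + Σ_{s≥2} (t_s − t_1) × D_s.

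So LOCI lies in the span of the intercept and the site dummies. A workgroup random effect or a log link does not change this, because the redundancy is in the fixed part of the linear predictor. Agency dummies are also redundant beside a full site set, since sites nest in agencies.

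**Rank check.** Number of sites = (60 − co-located workgroups) + shared sites. Residual SS is the variation in LOCI left after the other columns. An evenly split 60-workgroup design has 60 × 0.5 × 0.5 = 15. Ranges are over 5, 10 and 15 agencies.

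| Co-location | Sites | Rank without → with LOCI, all site dummies | 60 − rank | Residual SS, agency dummies only | Residual SS, agency plus shared-site dummies |
|---|---|---|---|---|---|
| one site of 3 | 57 + 1 = 58 | 58 → 58 | 2 | 14.67–14.88 | 14.00–14.18 |
| one site of 2 | 58 + 1 = 59 | 59 → 59 | 1 | 14.87–14.96 | 14.33–14.45 |
| two sites of 2 | 56 + 2 = 58 | 58 → 58 | 2 | 14.73–14.92 | 13.67–13.91 |
| three sites of 2 | 54 + 3 = 57 | 57 → 57 | 3 | 14.60–14.83 | 13.00–13.41 |

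1. *All site dummies, Aim 3.* The rank does not move in any of the 12 layouts, for 60 workgroup rows (SIC) or 360 provider rows (time-averaged fidelity). The residual SS of LOCI is zero to machine precision (below 1e-26).
2. *Agency dummies only.* Adding LOCI raises the rank by 1 in all 12 layouts (5 → 6, 10 → 11, 15 → 16), and almost all of the 15 is retained.
3. *Dummies for shared sites only.* The rank again rises by 1. Relative to agency dummies only, residual SS falls by between 1 − 14.45/14.96 = 3% and 1 − 13.00/14.60 = 11%. That loss arises because the co-located workgroups drop out of the contrast.
4. *Aims 1 and 2.* With five waves (0, 4, 8, 12 and 16 months) and all site dummies, adding Time × LOCI raises the rank by 1 (for example 59 → 60). The interaction is estimable.

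**The case against.** The strongest reply is that a full set of dummies was not meant. One of the two reasons given for them is that some workgroups share a site, which concerns only about 5% of workgroups. Agency dummies would be pointless beside a full site set, yet both are listed. A full set would also come close to a fixed effect for every workgroup, yet workgroup is kept as level 3. All three facts fit dummies for shared sites only, and then LOCI is estimable. This objection stands in part: the restricted reading is plausible, so the aliasing cannot be stated as unconditional. But the text does not state the restriction, and under it the co-located workgroups still contribute nothing to Aim 3.

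Other replies carry less weight.
- H3a speaks of improvement and sessions are coded monthly, so fidelity might be modelled with a time term. The analysis text, however, averages it over time, and a time term for fidelity would not help the SIC.
- The negative binomial model is introduced separately without a covariate list, so applying the dummies to it is an inference, though one that the phrase covering all analyses invites.
- The SIC yields scores within each of eight stages, so one record per workgroup is an assumption. It affects the count of 57–59 parameters for 60 records but not the aliasing, because condition still does not vary within a site.
- The section also calls randomization workgroup-level. That does not rescue the model, since co-located workgroups share a condition.

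A reader might infer that the trial cannot answer Aim 3, or that all its analyses fail. The documents support neither: the data do identify the effect once the site dummies are removed or restricted, and Aims 1 and 2 keep their target.

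**Conclusion.** The point holds conditionally. If every site gets a dummy, as the sentence literally reads, H3a and H3b have no estimable LOCI effect; this follows from site-level allocation alone and does not depend on the number of agencies, the ICC or the effect size. If only shared sites get a dummy, the effect is estimable, at a cost of about 3% to 11% of the variation in LOCI under the assumed layouts. The Time × Intervention test in Aims 1 and 2 is estimable either way. The site counts (57–59) and the SIC layout are assumptions used for illustration. The text needs correcting because the two readings lead to opposite outcomes for Aim 3 and it does not choose between them.

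**What to change.** For the Aim 3 models (fidelity and SIC), remove the site dummies and keep agency as a fixed effect. Handle the roughly 5% of co-located workgroups by clustering at site, the randomized unit: either one site-level random effect or site-clustered standard errors, with a small-sample correction. Do not require separate site and workgroup variance components. With 57–59 sites for 60 workgroups, only 60 − 59 = 1 to 60 − 57 = 3 degrees of freedom separate the two.

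For Aims 1 and 2 the same change is optional, for consistency across models. If the intention was to give dummies only to shared sites, the text should say so and acknowledge that those workgroups then add nothing to the Aim 3 comparison.

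The cost is a change of wording in the analysis section or the SAP. No new data are needed.
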